## Abstract

Background: Urinary incontinence (UI) is a common health problem and seriously affects quality of life. Many women lack understanding of UI or are too ashamed to seek medical advice early, leading to a low treatment rate. The aim of this study is to establish an effective UI progress prediction model for elderly women with UI for earlier detection and better treatment. Methods: This study is conducted as a prospective, multi-center, cohort study, and recruits 800 women aged ≥60 with mild or moderate UI in China. Participants are divided into three groups: stress urinary incontinence group (SUI), urgency urinary incontinence group (UUI), and mixed urinary incontinence group (MUI). This study will investigate the general conditions of patients, after complete relevant pelvic floor function assessment, as well as after follow up at 6 months, 12 months, and 18 months by telephone. The primary endpoint is UI disease progress. Single factor and multi-factor Cox regression model analyses are undertaken to evaluate the associated risk factors affecting the progress of UI to establish a progress prediction model for elderly women. Discussion: This study will provide more predictive information for elderly women with UI, and new clinical references for the intervention and the treatment of UI for medical staff.

## 1. Background

Urinary incontinence (UI) is defined as an abnormal urinary control condition in which urine flows out of the urethral opening involuntarily [1]. It is common lower urinary tract symptom in women and one of the most frequently reported diseases associated with pelvic organ prolapse in adult women. UI can occur in all age groups, whereas it is more commonly seen in middle-aged and elderly patients. The globally reported UI prevalence in women ranges from 25% to 45% and increases year by year [2], and the prevalence of UI among adult women over 60 years old has been reported to be up to 38% [3]. Similarly, the reported UI prevalence in Chinese adult women differs from 8.7% to 69.8%, while that in older Chinese women reaches 16.9% to 61.6% [4]. UI is etiologically and pathophysiologically categorized for three types, as follows: stress urinary incontinence (SUI), urgency urinary incontinence (UUI), and mixed urinary incontinence (MUI) [5]. SUI is the most common type, accounting for 50% of all UI cases [6,7], and is defined as involuntary urinary leakage when physical exertion from coughing, sneezing, or laughing causes pressure to the bladder. Inadequate support of the urethra by the pelvic floor muscles and deficiency of the urethral intrinsic sphincter are the recognized essential mechanisms for UI. The reported UI-associated factors include patient age, body mass index (BMI), genetic factors, smoking, race, constipation, pregnancy and multiple childbirths, previous pelvic floor operations (e.g., hysterectomy), and hormone deficiency or menopause, all of which cause pelvic floor muscle weakness [3,8,9]. UUI prevalence has been reported in many studies to be between 1% to 7% [6,7], which is much lower than UI. UUI generally refers to an overactive bladder caused involuntary urinary leakage with urgency, which is usually caused by involuntary contractions of the bladder wall detrusor muscle. UUI may be triggered by simple daily phenomena and activities such as the sound of tap water, exposure to low temperatures, or drinking cold drinks, and has several congenital causes including myogenic, neurogenic, and urethral symptoms [3,8,10]. MUI is a mixture of symptoms of SUI and UUI, with a reported incidence of 7.5% to 25%, secondary to SUI [6,7]. Its etiology is also a combination of factors causing SUI and UUI [11,12].

UI in women is a huge global health problem. Besides affecting women’s quality of life by limiting social activities, productivity, and social and sexual behaviors, it also has significant impacts on medical costs and even increases financial burden on women and society [4,13]. In addition, regarding the psychological impact of UI on women, numerous research works claim that it creates a long-term period of mental suffering, such as depression or anxiety [14,15,16]. However, some scholars have found, through study of female athletes, that UI does not cause depression and anxiety. Such conclusions are most possibly related to the study subjects, namely female athletes, who have an acknowledged relationship between UI and sport, with most suffering mild UI, as well as having a stronger sense of happiness because of their sport, thus UI might not impact their psychological mode [17].

UI as a common public health issue, is a worldwide problem that has not been indicated to most women, and thus not enough attention has been paid to its early diagnosis and treatment. The impacts of mild and moderate to severe UI on quality of life are greatly different. Although mild UI has little impact on quality of life, as it becomes more severe, it will not only worsen quality of life, but will also bring heavy financial burden to the family and society. Therefore, it is important to use early interventions to upgrade patients’ quality of life and reduce the financial burden related to this disease by detecting any risk factors from patients with mild UI, so as to prevent their mild UI from progressing to moderate or severe.

The common interventions for the prevention of UI include lifestyle intervention, pelvic floor muscle training, biofeedback therapy, and electrical stimulation therapy, etc. However, all these interventions lack standard and systematic evaluations of their preventive effectiveness [18,19].

With the increasing popularity of big data technology, using machine learning to measure the situation and to predict the development of diseases closely related to human health has globally become a hot research topic and application field recently. At present, there is a precedent of using clinical diagnostic software based on large-scale epidemiological data analysis to predict the incidence of diseases in the world. A well-known prognostic model is the Framingham risk score, which predicts the risk of cardiovascular disease in 10 years [20]. Current studies on UI are all disease pathogenesis models, and there are no reports on UI development or the application of any prediction model or software for UI progress in elderly women.

The aims of this study are to systematically investigate the disease progress related factors for elderly women with UI, so as to establish a UI progress prediction model and to improve science-based interventions and preventive measures for UIs [19,21].

## 2. Materials and Methods

### 2.1. Study Design and Setting

The study is conducted as a prospective multicenter study to collect epidemiological factors for the analysis of the impacts of physical activity, chronic diseases, pregnancy and delivery, genetic characteristics, pelvic floor function assessment (e.g., pelvic floor muscle strength, pelvic floor ultrasound, pelvic floor electrophysiology, and morphology index), and other factors in elderly women. Data analysis will be conducted by means of bioinformatics and mathematical modeling objectives to investigate the influence of UI progress and prognosis related factors, and to construct a prediction model of UI progress in elderly women. This study is carried out by Peking University People’s Hospital in Beijing, in cooperation with Wuhan University People’s Hospital in Wuhan, China. A total of 800 patients will be recruited, 400 from Beijing and 400 from Wuhan. Four district-level hospitals in Beijing are involved as the sub-centers in Beijing, namely Tongzhou District Maternal and Child Health Care Hospital, Fengtai District Maternal and Child Health Care Hospital, Fangshan District Maternal and Child Health Care Hospital, and Changping District Maternal and Child Health Care Hospital. Two district-level hospitals in Wuhan are involved as the sub-centers in Wuhan, namely Wuhan Qingshan District Maternal and Child Health Hospital and Wuhan East Lake New Technology Development Zone Fozu Mountain Community Health Service Center. Each sub-center will select communities within the district that are targeted to recruit elderly female patients who are ≥60 years of age with mild to moderate UI by distributing a research subject leaflet. Eligible women need to sign informed consent before being enrolled in the cohorts. Figure 1 illustrates the flow diagram of the study for all subjects.

### 2.2. Participants

The project is approached by phone calls to women ≥60 years of age (the elderly women) and were recently diagnosed with mild or moderate UI. A primary screening survey is conducted during the approach by asking the women three simple questions by investigators: whether they have urine leakage, what is the urine leakage frequency, and what accompanying symptoms they have. Women who are primarily screened to have potential mild and moderate UI will be invited for further examination at the hospitals, where the preliminary examination will be conducted by trained doctors while recording the detailed patient’s history.

#### 2.2.1. Inclusion Criteria

Participants will be enrolled if they are: (1) ≥60 years of age; (2) educated enough to complete the questionnaires; (3) able to move freely to attend a hospital examination; (4) previously diagnosed as mild and moderate UI, including SUI, UUI, and MUI; (5) suffering urine leakage during occasional coughing, exertion, sneezing, fast walking, and other abdominal pressure; or (6) suffering frequent and urgent urination with urinary leakage and nocturia.

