### 2.6. Initial Screening, Assessment, and Follow-Up

After informed consent, participants will be arranged in the hospital in batches. The patients will be received by a team that consists of physicians specialized in the pelvic floor and nurses. All investigators of the team are comparatively fixed and need to be trained by a principal investigator from Peking University People’s Hospital on the research protocol, the inclusive and exclusive criteria, and the questionnaire interviewing. Roleplay on questionnaire interviewing was conducted to have each of the team members interview a provider’s female family member who had no idea about the study, under the supervision of the principal investigator, to confirm that the question was raised using publicly understandable terms and to avoid inducive wording. Questionnaires to the participants will be completed via interview in a doctor’s office at the clinic, which will be specially resettled for allowing participants to be interviewed under a comfortable circumstance so as to avoid answer bias from patient nervousness.

Every participant will be given a unique study ID. Participants’ demographic information, including age, marital status, education level, occupation, BMI, living habits, menstruation, marriage, childbirths, sex life status, and chronic diseases, ect, were collected confidentially. Participants will be primarily grouped according to the questionnaire interview at the enrollment visit by the investigators. Included in the questionnaires are relevant questions regarding inclusive criteria for three types of UI, which were designed according to the UI classification of the International Continence Society [1]. Participants will be included in the SUI group if question 5 is satisfied, in the UUI group if question 6 is satisfied, or in MUI if question 5 and 6 are both satisfied. All the communication between providers and participants during the questionnaire interview will be monitored by the PI and will be fully recorded for quality control analysis.

For grouping the participants, we will grade the disease situation for each of the participants grouped in each of the groups according to the symptoms using the Ingelman-Sundberg Indexing method and International Continence Society standards [1]. Grading criteria are listed in the following form (Table 1): Participants will be excluded if they are graded to have severe UI.

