After collecting the above-mentioned data, all participants will completed a gynecological examination, one-hour urinal pad test, pelvic floor electrophysiological examination, uroflowmetry, pelvic floor ultrasound, and morphological examination (Table 2). All the examinations will be conducted by the teams, using the same model instruments to avoid data biases, and data will be recorded on tablets connected to the database. The items to be inspected are as follows:(1)**Gynecological examination** includes uterus, vagina and appendages inspections; pressure inductive testing; bladder neck elevation testing; hand Oxford muscle strength classification testing; pelvic organ prolapse quantification (POP-Q); and one-hour urinal pad testing.(2)**UI questionnaires** concerning International Consultation on Incontinence Questionnaire-Short Form (ICIQ-SF) for investigation of UI frequency, degree, and its impacts on quality of life via 0–21 scoring to represent the severity of the UI [22]; OABSS questionnaire for assessment of the symptoms of the participants whose bladders are overactive and the severities of their urinary frequency, nocturia, urinary urgency, and urinary incontinence via scoring 0–15 to indicate the lowest to highest severity [23,24]; and Urogenital Distress Inventory-6(UDI-6) for evaluation of the lower urinary tract dysfunction via scoring 0–24 to present the severity of the urinary incontinence [25,26].(3)**Pelvic floor electrophysiological examination** on an instrument to collect data regarding indicators such as the maximum vaginal dynamic pressure, the vaginal resting pressure, the strength grades of type I and type II muscle, and the fatigue of type I and type II muscle fibers.(4)**Uroflowmetry** on the maximum and average rate of urine flow, urination time, and the urine flow curve.(5)**Pelvic floor ultrasound examination** performed by two attending doctors who have rich clinical experience of pelvic floor ultrasound for the residual urine, detrusor muscle thickness, bladder neck movement, urethral rotation angle, bladder posterior angle, the shape of the internal urethra opening, the distance from the lowest point of the bladder to the posterior lower edge of the pubic symphysis, levator ani muscle trauma, and levator ani hiatus area in the Valsalva status.(6)**Morphological examination** a study reported that the pelvis architecture was closely related to UI in women, especially pelvic inlet and pelvic outlet diameters as risk factors for UI [27], therefore, we include pelvic floor morphology into the study, which mainly includes the inclination angle of the sacrum and the anterior superior iliac spine, and the pelvic tendency.

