## Figures and Tables

**Figure 1 ijerph-19-00734-f001:**
[figure not shown]
Study flow chart.

**Table 1 ijerph-19-00734-t001:** Diagnosis criteria for subtypes of UI.

UI Types	Grade	Criteria
SUI grading	Mild	UI appears when coughing or sneezing without the need for a urinal pad
	Moderate	UI appears when running, jumping, or fast walking, and a urinal pad is needed
	Severe	UI appears when changing body position or resting at bed
UUI grading		According to OABSS indicators Question 3 (urgency) has a score of 2 or more, and the total score is 3 or more)
	Mild	3 ≤ score ≤ 5
	Moderate	6 ≤ score ≤ 11
	Severe	Score ≥ 12
MUI grading		According to the grade of SUI and UUI related symptoms, highest grading to be matched

UI: urinary incontinence; SUI: stress urinary incontinence; UUI: urgency urinary incontinence; MUI: mixed urinary incontinence; OABSS: overactive bladder symptom score.

**Table 2 ijerph-19-00734-t002:** Participant baseline screening, assessment, and follow-up schedule.

Characteristics	Baseline			Follow-Up (6 Months, 12 Months, 18 Months)		
	SUI	UUI	MUI	SUI	UUI	MUI
Age (≥60)	•	•	•			
Race	•	•	•			
Marital status	•	•	•			
Educational level	•	•	•			
Mainly physical labor	•	•	•			
BMI	•	•	•			
Parity	•	•	•			
Manner of delivery	•	•	•			
UI during pregnancy	•	•	•			
UI after childbirth	•	•	•			
Menopause	•	•	•			
Sex life	•	•	•			
Drink preference	•	•	•			
24-h Volume of liquid intake (mL)	•	•	•			
Smoking	•	•	•			
Comorbidities	•	•	•			
Chronic cough						
Asthma						
Diabetes						
Constipation						
Pelvic inflammatory disease	•	•	•			
Depression	•	•	•			
Urinary tract infection (last 4 weeks)	•	•	•			
History of gynecological surgery	•	•	•			
Family history of UI	•	•	•			
UI duration (year)	•	•	•	•	•	•
Frequency of urine leakage (time/month)	•	•	•	•	•	•
Symptoms accompaning urine leakage	•	•	•	•	•	•
Using urine pads (per/month)	▲	▲	▲	▲	▲	▲
Impact on life	•	•	•	•	•	•
POP-Q	•	•	•			
Hand test Oxford muscle strength grading	•	•	•			
One-hour urine pad test (g)	•	•	•			
Severity of UI	•	•	•	•	•	•
Mild						
Moderate						
Severe						
Pelvic floor electrophysiology examination	•	•	•			
Uroflowmetry	•	•	•			
Pelvic floor ultrasound	•	•	•			
Morphological examination	•	•	•			
ICIQ-SF score	•	•	•	•	•	•
OABSS score	•	•	•	•	•	•
UDI-6 score	•	•	•	•	•	•
UI progress				▲	▲	▲

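### Inclusion criterion 6, which also assigns the UUI and MUI groups, is narrower than the article's own description of UUI and its Table 1 threshold

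*Protocol article*

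**What the plan says.** Four places in the protocol article bear on who counts as having urgency incontinence.

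- Section 1 (Background): "UUI generally refers to an overactive bladder caused involuntary urinary leakage with urgency". Frequency and nocturia are not part of this description.
- Section 2.2.1, criterion 6: "6) suffering frequent and urgent urination with urinary leakage and nocturia". Four symptoms are listed.
- Section 2.6 assigns groups from the matching questionnaire items: women go "in the UUI group if question 6 is satisfied, or in MUI if question 5 and 6 are both satisfied". Item 5 alone gives SUI.
- Table 1 sets the UUI threshold on the OABSS: "Question 3 (urgency) has a score of 2 or more, and the total score is 3 or more". Totals of 3 to 5 are mild and 6 to 11 moderate. Frequency and nocturia have no minimum.

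Section 2.6 describes the OABSS as covering "the severities of their urinary frequency, nocturia, urinary urgency, and urinary incontinence via scoring 0–15", the same four symptoms that criterion 6 lists. According to the Abstract, the study "recruits 800 women aged ≥60 with mild or moderate UI in China".

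Section 2.7 makes the endpoint depend on the group. SUI is judged on a change of leakage trigger, a new need for pads, or an ICIQ-SF rise of at least 4. UUI is judged on an OABSS rise or a new need for pads. MUI is judged on any of these.

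**The concern.** Criterion 6 does two jobs: it opens the urgency route into the study and it sorts women into groups. If it asks for more than the Background and Table 1 ask for, two things can follow.

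First, some women whom Table 1 would grade as mild UUI may not be admitted, because they do not void often or do not get up at night. Section 1 gives the prevention of progression from mild disease as the study's rationale, so a cut at the lower end of the severity range works against that purpose.

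Second, a woman with both stress and urgency leakage but no nocturia would be filed as SUI. Worsening of her urgency component would then count only if it showed as a new need for pads, a change of trigger or a sufficient ICIQ-SF rise. An OABSS rise alone, which would count in MUI, would not. That would be outcome misclassification in the primary endpoint of the prediction model.

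**Working it through.** The article computes no figure on this point. The Table 1 cut-offs are definitions and have nothing to reproduce. The check is whether criterion 6 and Table 1 can describe the same women.

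**Inputs from the article.** Four OABSS domains with a total of 0 to 15 (section 2.6); urgency item at least 2, total at least 3, mild band 3 to 5 (Table 1); the four symptoms in criterion 6 (section 2.2.1).

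**Assumptions not in the article.** A symptom that is present scores at least 1. Item maxima are 2 (frequency), 3 (nocturia), 5 (urgency) and 5 (leakage), which sum to 15. Two other splits of the 15 points, 3/3/4/5 and 4/4/4/3, gave the same counts of 15 and 1 for the first two rows below.

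**Lowest total** = frequency + nocturia + urgency + leakage, with leakage at least 1 and urgency at least 2. The last column counts item patterns with a total of at most 5.

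| Requirement | Lowest total | Mild totals reachable | Mild score patterns |
|---|---|---|---|
| Table 1 plus leakage | 0 + 0 + 2 + 1 = 3 | 3, 4, 5 | 1 + 4 + 10 = 15 |
| Criterion 6 read literally | 1 + 1 + 2 + 1 = 5 | 5 | 1 |
| Literal, frequency may score 0 | 0 + 1 + 2 + 1 = 4 | 4, 5 | 1 + 4 = 5 |
| Literal, frequency and nocturia may score 0 | 0 + 0 + 2 + 1 = 3 | 3, 4, 5 | 15 |

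In the moderate band (6 to 11), the literal reading leaves 90 of 191 patterns (102 of 191 and 110 of 177 under the other splits). All these counts are of score patterns, not women.

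**Grouping, traced through sections 2.6 and 2.7**, taking the questionnaire items to follow the criteria:

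- Urgency leakage, no nocturia, no stress leakage. Literally, neither item 5 nor item 6 is met, so she has no group. Table 1 would call her UUI if urgency scores at least 2 and the total is at least 3.
- Urgency and stress leakage, no nocturia. Literally only item 5 is met, so she is SUI. The Background and Table 1 would make her MUI. An OABSS rise does not count as progress for her.
- Stress leakage and nocturia, no urgency. If the symptoms in criterion 6 are read as alternatives, items 5 and 6 are both met and she is MUI. Any OABSS rise then counts, although Table 1 would not call her urgency-incontinent.

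**Share of women affected.** Among women with mild UUI, the proportion failing the literal criterion is 1 − p, where p is the proportion with both frequency and nocturia. The article gives no value for p. As an assumption only, p from 20% to 80% gives 80% down to 20% failing, and some of these could still enter through criterion 5 in the wrong group.

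**The case against.** The strongest reply is that criterion 6 is a loose description of a symptom cluster, not a four-part test. The same list uses the conjunction carelessly elsewhere. Criterion 4 joins mild to moderate in a way no single woman could satisfy, and criterion 5 reads "suffering urine leakage during occasional coughing, exertion, sneezing, fast walking, and other abdominal pressure", where any one trigger must be meant. This stands as a reason to call the wording ambiguous. It does not cure the problem, because reading the symptoms as alternatives lets stress leakage with nocturia count as MUI. Neither reading gives the Background's description of UUI.

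Other parts of the reply also stand:

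- Question 6 itself is not reproduced. Section 2.6 says that the items were designed from the International Continence Society classification, so that question 6 repeats criterion 6 word for word is an inference.
- The only connector in the inclusion list comes before item 6, so how criteria 4, 5 and 6 combine is not stated. A woman with a recorded UUI diagnosis is not certainly ineligible.
- Entry criteria may be narrower than a general disease description. The sharper conflict is with Table 1, which is headed as diagnostic criteria and has no frequency or nocturia requirement.
- The minimum of 5 depends on item scoring that the article does not give.

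A reader might infer from the fall from 15 patterns to 1 that most women with mild urgency leakage are barred, or that the UUI group will hold almost no mild cases. The article does not support this. Score patterns are not equally likely, and no prevalence of frequency or nocturia in this age group is given. Nor does it follow that progress from mild UUI cannot be estimated, since a total of 5 is still mild. Frequency and nocturia would still vary in degree among the women admitted, so their predictive value would be reduced, not removed.

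**Conclusion.** The point holds as an inconsistency between section 2.2.1 and its use in section 2.6 on one side, and the Background and Table 1 on the other. Its size is known only in scores. With every listed symptom scoring at least 1, two of the three mild totals are lost. With frequency allowed to score 0, one is lost. With both frequency and nocturia allowed to score 0, none is. The number of women kept out or misgrouped is unknown. The grouping consequence needs no scoring assumption, but it does assume that question 6 follows criterion 6. The target population is mild or moderate UI of all three types, so this affects the urgency and mixed groups and does not undermine the study as a whole. It merits correction because it touches both group assignment and the primary endpoint, and because correcting it is cheap.

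**What to change.** Reconcile criterion 6 and the grouping question with the Background and Table 1. Let UUI, and the urgency part of MUI, rest on leakage with urgency plus the Table 1 OABSS threshold. Record frequency and nocturia as baseline variables and do not require them for entry or grouping. State how criteria 4, 5 and 6 combine.

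The cost is one reworded criterion and one reworded questionnaire item, with no added visits. Women already enrolled would be regrouped from the baseline OABSS. Table 2 makes the OABSS mandatory at baseline and at follow-up in all three groups, so their progress can be judged again under the right criteria. Regrouping does not recover women already turned away under the literal wording.
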